### Control group

In nursing homes that are randomized to the control condition, care will be provided as usual. In case nursing home staff in this group receives training regarding ACP and/or or initiate ACP with residents or families, these nursing homes will remain in the control group. We will perform baseline and follow-up measurement of primary and secondary outcomes in this group, but no process evaluation assessments as the intervention is not delivered there. After the study ends, the control nursing homes will have the possibility of discussing the results of the study with the research team, have access to all intervention materials and receive a one-day training from the external trainers.

### Outcomes

#### Primary outcome

The two primary outcomes are: 1) nursing home care staff’s knowledge of ACP and 2) nursing home care staff’s confidence in their own skills regarding ACP (self-efficacy). These outcomes are measured at baseline (T0) and after eight months (T1). We assess knowledge and self-efficacy as these are identified as necessary intermediate steps for healthcare professionals to be able to actually engage in ACP, according to both social cognitive theory and literature about successful ACP [9, 10, 27].

#### Secondary outcomes

The following secondary outcomes are measured at baseline (T0) and after eight months (T1): 1) nursing home care staff’s attitudes towards ACP and ACP practices; 2) support staff’s and volunteers’ ACP practices; and 3) support staff’s and volunteers’ self-efficacy. Outcomes on support staff- and volunteer level were added because an important part of the ACP intervention is targeting these professional roles. The outcome measure was adapted to this population (See Additional file 1).

#### Outcome measurements

To evaluate ACP knowledge, attitudes, self-efficacy and practices, we developed a questionnaire, based on the questionnaire in a study from Detering et al. [28], which was translated via forward-backward translation and adapted to fit the local context. Items were added based on the Questionnaire Tool for Registered managers from Ulster University [29] and expertise of the multidisciplinary author group. The adapted version of the questionnaire was tested with six researchers who have clinical practice experience with older patients (three registered nurses, one GP, one psychologist and a nursing home volunteer), and through an online survey with 107 healthcare professionals and volunteers active in the Flemish nursing home setting. All items were reviewed and discussed within the author group and questions related to legal issues were additionally reviewed by an expert in Medical Law. Results of this trial will be based on the final version of the questionnaire (Additional file 1).

In the knowledge section of the final version of this questionnaire, respondents are asked to respond to 11 statements (e.g. ‘a nursing home resident can only assign a family member to be his/her legal representative’) ‘true’, ‘false’ or ‘I don’t know’. The self-efficacy section asks respondents to indicate how confident they feel (10-point Likert scale, ranging from ‘little confidence’ = 0 to ‘a lot of confidence’=10 and ‘not applicable’) regarding 12 items (e.g. ‘how confident do you feel about: initiating ACP conversations?’). In the attitudes section respondents are asked to indicate how strongly they agree or disagree (5-point Likert scale ranging from ‘completely disagree’ = 0 to ‘completely agree’ = 5) with 12 statements (e.g. ‘in most cases nursing homes residents do not know enough about healthcare to construct an advance directive’). The construct ACP practices asks about ACP activities in the past six months (e.g. initiating an ACP conversation, drafting of an advance directive, etc). For support staff and volunteers the ‘self-efficacy’ and ‘ACP practices’ sections are adapted to include three items evaluating ‘self-efficacy’ and two items to evaluate ‘ACP practices’. These items are all based on the main questionnaire. Table 2 provides a full overview of outcomes and measures. Questions and scale metrics of the measures are provided in Additional file 1.

**Table 2 Tab2:** Outcomes and outcome measures of ACP+ trial

Outcome	Respondent	No. of items	Item example(s)
Knowledge of ACP	Nursing home care staff (primary outcome)	11 items*	“A resident can only assign a family member as his/her legal representative”
Self-efficacy towards ACP	Nursing home care staff (primary outcome)	12 items†	“Point out how much confidence you have in your own skills with regard to the following activities/roles: To explain the role of a legal representative to residents and family”
	Support staff	3 items†	“Point out how much confidence you have in your own skills with regard to the following activities/roles: To talk about wishes regarding future care with family members and residents”
	Volunteer	3 items†	Same as above
Attitudes towards ACP	Nursing home care staff	12 items‡	“GPs should be involved actively to help residents draft an advance directive”
ACP practices	Nursing home care staff	8 items	“Did you start an ACP conversation the past six months?”
	Support staff	2 items	E.g. 1: “In the past six months, did you talk with a resident about the next themes: future care and his/her related wishes, dying and death, advance directives?” E.g. 2: “In the past six months, did you talk with a family member or next-of-kin of a residents, about the next themes: future care and his/her related wishes, dying and death, advance directives?”
	Volunteer	2 items	Same as above
Demographic and background information	Nursing home care staff		Age, gender, date of today, number of years working experience in direct patient care, number of years employment in nursing home sector, current function in the facility, highest education, number of hours working in the nursing home per week, whether or not they received training in palliative care or ACP, average number of residents for which they care on regular working day.
	Support staff		Age, gender, date of today, number of years working experience in direct patient care, number of years employment in nursing home sector, current function in the facility, highest education, number of hours working in the nursing home per week, whether they received training regarding one of the following themes: vision and values of the nursing home, palliative care, communication skills, information transfer about resident to other care staff, ACP, other; if they had a personal conversation with a resident that has dementia or Alzheimer’s.
	Volunteer	7 items	Age, gender, date of today, employment status, highest education, number of years active as volunteer, number of years active as volunteer in this nursing home
Structural facility-level characteristics	Key contact person in nursing home	21 items	Type of facility, number of beds recognized by government, number of beds available, number of beds occupied, number of residents per KATZ scale category, umbrella organisation, with which electronic resident file system they work (e.g. GERACC, Care Solutions or others), number of residents died over past six months, average time of stay, availability of specific written guidelines available about palliative care or ACP, availability of patient-specific forms regarding ACP, % of residents died in nursing home, % of residents that has an up-to-date plan regarding end-of-life care, number of residents with written AD, regular multidisciplinary team meetings, number of staff: FTE and heads, number of volunteers registered in nursing home, number of hours per week the coordinating advisory physician is present in facility, number of GPs involved with patients in nursing home

*ACP* advance care planning; *GP* general practitioner; *FTE* full-time equivalent; *AD* advance directive; *KATZ* index of independence in activities in daily living; *GERACC* software package for nursing homes in Belgium

*Response categories: ‘True’, ‘False’ or ‘I don’t know’

†Response categories: 10-point Likert scale, ranging from ‘little confidence’ (=0) to ‘a lot of confidence’ (=10) and ‘not applicable’

‡Response categories: 5-point Likert scale ranging from ‘Completely disagree’ (=0) to ‘Completely agree’ (=5)

§Response categories: ‘Yes’ or ‘No’

#### Other measures

We additionally measure several structural facility-level characteristics of participating nursing homes, and demographic and background information in all participating staff and volunteers. These characteristics are described in Table 2.

### Process evaluation

Via an in-depth process evaluation in the intervention group we will assess:
*implementation*: defined as the process through which interventions are delivered, and what is delivered in practice [17]. Outcomes involve: how delivery is achieved and what is delivered (dose, reach, fidelity, adaptations).*mechanisms of impact*: the intermediate mechanisms through which intervention activities produce intended (or unintended) effects [17]. This involves: responses and interactions from participants with the mediators that might explain changes in outcomes and unanticipated pathways or consequences.*context*: factors external to the intervention that may influence its implementation or whether mechanisms of impact act as intended, including outcomes such as contextual moderators (barriers and facilitators) and participant’s intention for maintenance [17].

The process evaluation has a mixed-methods design combining quantitative and qualitative research methods, collected regularly before, throughout and after the intervention period. The results of this process evaluation will enable us to strengthen the links in the theoretical model we have developed in a previous phase [10]. An overview of the process evaluation outcomes (implementation, mechanisms of impact, context) and data collection methods can be found in Table 3.

**Table 3 Tab3:** Process evaluation methods based on UK MRC guidance on process evaluations of complex interventions (Moore et al. 2012)

Dimension (definition*)	Subdimension (definition*)	Measurements	Data collection method (qualitative or quantitative; timing)
Implementation** (the process through which interventions are delivered, and what is delivered in practice)	HOW delivery is achieved (implementation process: structures, resources and mechanisms through which delivery is achieved)	- Resources: time spent by trainer on preparation and delivery of intervention - Resources: total trial cost associated with delivery of intervention (printing cost training materials, salary trainers, rent training locations and catering) - Implementation process of all ACP+ activities	- Structured diary filled in by trainers (quantitative; weekly) - Expenses from researchers and trainers (quantitative; continuous) - Semi-structured interviews with trainers (qualitative; every 4 months) - Semi-structured group interviews with ACP reference persons per IF (qualitative; after T1)
	WHAT is delivered (the quantity and quality of what is delivered) 1) Dose (how much intervention is delivered)	- Number and type of intervention activities‡ delivered in each IF	- Structured diary filled in by trainers (quantitative; weekly)
	2) Reach† (the extent to which a target audience comes into contact with the intervention)	- Number of ACP Reference Persons of each IF attending two-day training /total number of staff in each IF - Attendance rate of staff during in-house training sessions (for ACP Conversation Facilitators and ACP Antennas) in each IF/ total number of staff in each IF - Number of residents informed about ACP in each IF/total number of residents at T0 in each IF - Number of residents for whom a family member is informed about ACP in each IF/total number of residents at T0 in each IF - Number of GPs informed about ACP in each IF/total number of GPs at T0 in each IF - Number of volunteers informed in each IF/total number of volunteers at T0 in each IF - Number of residents or family members of residents offered minimum one ACP conversation/total number of residents at T0 in each IF - Number of residents with an advance directive/total number of residents at T0 in each IF	- Attendance lists (quantitative; before start of each training or information session) - Survey about number of residents, family and volunteers informed, to be filled in by key contact person in IF (quantitative; after month 6 and at the end) - Information provided by key contact person in IF, based on ACP+ registry document (quantitative; continuous) - Facility level data (quantitative; T1)
	3) Fidelity (the consistency of what is implemented with the planned intervention)	- Number of activities delivered as intended (dose delivered as intended) in each IF/total number of activities - Type of activities delivered, according to participating staff - Content and quality of training workshops for ACP Reference Persons delivered as intended, as observed by researchers - Number of ACP Reference Persons per IF that attended training session scored high on fidelity/total number of care staff at T0 in each IF - Median score of trainer competencies for each training (across and in each IF) - Median score of quality of each training (across and in each IF)	- Structured diary filled in by trainers (weekly) - Semi-structured interview with trainers (qualitative; every 4 months) - Two post-intervention focus group with trained staff across IF (qualitative; after T1) - Semi-structured group interview with ACP Reference Persons in each IF (qualitative; after T1) - Observation of two-day training for ACP Reference Persons by researchers, using checklist of minimum requirements and overall rating of fidelity and quality (quantitative) - Attendance list (quantitative; at each ACP+ training) - Post training survey for participants (quantitative; after each ACP+ training)
	4) Adaptations (alterations made to an intervention in order to achieve better contextual fit)	- Adaptations made to activities of the ACP+ activities (e.g. number, duration, content), according to trainers and Trial Monitor - Experiences with of participants regarding adaptations made and the contextual fit of activities of the ACP+ programme	- Semi-structured interview trainers (qualitative; every 4 months) - Semi-structured group interview with ACP Reference Persons in each IF (qualitative; after T1) - Notes made by Trial Monitor based on communication with trainers and IFs
Mechanisms of impact (the intermediate mechanisms through which intervention activities produce intended (or unintended) effects)	Responses and interactions (how participants interact with the intervention)	- Staff experiences with and views with regard to the ACP+ intervention and activities	- Semi-structured interview with one manager per IF (qualitative; after T1) - Two post-intervention focus group with trained staff across IF (qualitative; after T1) - Semi-structured group interview with ACP Reference Persons in each IF (qualitative; after T1)
	Mediators (intermediate processes which explain subsequent changes in outcomes)	- Evaluation of perceived mediators (or preconditions 1, 2, 6, 7 and interventions 1, 2, 3A, 3B, 4A, 4B, 4C, 6A, 6B, 8 in Theory of Change map [10]), as intermediate processes that might explain changes in outcomes.	- Semi-structured interview with one manager per IF (qualitative; after T1) - Two post-intervention focus group with trained staff across IF (qualitative; after T1) - Semi-structured group interview with ACP Reference Persons in each IF (qualitative; after T1)
	Unanticipated pathways or consequences†	- Potential unanticipated consequences of the ACP+ programme in residents and/or family, in staff, in GP according to participants	- Semi-structured interview with one manager per IF (qualitative; after T1) - Two post-intervention focus groups with trained staff across IF (qualitative; after T1) - One post-intervention focus group with ACP Reference Persons across Ifs (qualitative; after T1) - Three semi-structured interviews with residents and family in each IFs (qualitative; after T1)
Context (factors external to the intervention which may influence its implementation, or whether its mechanisms of impact act as intended)	Contextual moderators† potentially inhibiting or facilitating the implementation, organisation, sustainability and outcomes of ACP	- Contextual barriers and facilitators for 1) implementation (‘the process through which interventions are delivered, and what is delivered in practice’), according to participants - Contextual barriers and facilitators for 2) sustainability (‘the potential for an intervention to become part of routine practice’), according to participants - Contextual barriers and facilitators for 3) outcomes (knowledge, attitudes, self-efficacy and practice), according to participants	- Semi-structured interview with one manager per IF (qualitative; after T1) - Two post-intervention focus groups with trained staff across IF (qualitative; after T1) - Semi-structured group interview with ACP Reference Persons in each IF (qualitative; after T1) - Semi-structured interviews trainers (qualitative; every 4 months)
	Intention for Maintenance† (extent to which the programme is intended to be part of routine organisational practice and policy)	- Staff’s intention for performing ACP+ activities in the future - Organisational intention for long-term implementation - Participants’ recommendations for improving sustainability	- Semi-structured interview with one manager per IF (qualitative; after T1) - Semi-structured group interview with ACP Reference Persons in each IF (qualitative; after T1)

*ACP* advance care planning; *IF* intervention facility; *GPs* general practitioners

Types of training activities: 1) Two-day training for *ACP* Reference Persons (delivered by *ACP* Trainer), across all intervention nursing homes; 2) Two training sessions of each two hours for *ACP* Conversation Facilitators (delivered by *ACP* Reference Persons, supported by *ACP* Trainer), in-house; 2) One training session of 1,5 h for ACP Antennas (delivered by *ACP* Reference Persons, supported by *ACP* Trainer), in-house

*Definition by the MRC Framework by Moore et al. (2012)

**The term implementation is used within complex intervention literature to describe both post-evaluation scale-up (i.e. the ‘development-evaluation-implementation’ process) and intervention delivery during the evaluation period. Within this document, discussion of implementation relates primarily to the second of these definitions (i.e. the quality and quantity of what is actually delivered during the evaluation)

†Added by the research team

**Table 4 Tab4:**
[figure not shown]
Schematic overview of the ACP + programme. ACP advance care planning; BoD board of directors; CAP coordinating advisory physician; ACP Ref Person advance care planning reference person; GP general practitioner. *Decision-makers are head of nursing staff, head of residents’ care, nursing home management. All those involved with decision-making tasks in the nursing home.

### Sample size

When we assume unequal cluster sizes with a coefficient of variation of 0.17 and mean size of 30 and an intra-cluster correlation coefficient of 0.036 [30, 31], the design effect for a completely randomised cluster randomised trial is estimated at 2.07, and a sample of 161 staff members for each group across 6 clusters will achieve 80.27% power to detect an effect size of 0.5 at a significance level of 2.5%. This number has been increased to 242 staff members per group (total sample size of 484) to allow for an initial response rate of 70% and a staff turn-over of 10%. Current sample size calculation is valid for a completely randomised RCT (hence assuming a matching correlation of zero and assuming the intervention effect is constant across pairs). To compensate for the loss of degrees of freedom introduced by matching, it is suggested to add two clusters per arm [15].

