**Methods:**

We will conduct a cluster RCT in Flanders, Belgium. Fourteen eligible nursing homes will be pair-matched and one from each pair will be randomised to either continue care and education as usual or to receive the ACP+ programme (a multicomponent programme which is delivered stepwise over an eight-month period with the help of an external trainer). Primary outcomes are: nursing home care staff’s knowledge of, and self-efficacy regarding ACP. Secondary outcomes are: 1) nursing home care staff’s attitudes towards ACP and ACP practices; 2) support staff’s and volunteer’s ACP practices and 3) support staff’s and volunteers’ self-efficacy. Measurements will be performed at baseline and eight months post-measurement, using structured self-reported questionnaires. A process evaluation will accompany the outcome evaluation in the intervention group, with measurements throughout and post-intervention to assess implementation, mechanisms of impact and context and will be carried out using a mixed-methods design.

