#### Analysis

##### Outcome analysis

We will calculate summative scale scores for both primary and secondary outcomes. The resulting scale score for an individual is the sum of the individual item scores. For the knowledge items instructions are provided to check correct answers. If people answered, ‘I don’t know’, this will be scored as an incorrect item. The summative scale score of knowledge is sum correct knowledge items of 11 correct/incorrect answers. The summative scale score of ‘self-efficacy’ is the sum of self-efficacy items on a 10-point scale, ranging from 1 to 10, with 12 items. The primary statistical analyses will use an intention-to-treat (ITT) approach. In ITT the outcome data from all of the samples who were enrolled and randomised to the intervention or control group will be accounted for in the main analyses in the original groups to which they were randomised, regardless of whether or not they completed the ACP+ programme. We will fit a linear mixed model with condition, time and time*condition as fixed factors and with a random intercept for nursing home pair, random slope for time, condition and time*condition at the level of nursing home pair, random intercept for member, random slope for time at the level of member. The need for random slopes will be tested by comparing the difference between − 2 log (max) REML likelihoods with a $$ {\chi}_{1:2}^2 $$ distribution (using a mixture of chi-square distributions). In case of convergence issues, random slopes will also be left out of the model. Estimated cluster-adjusted means with corresponding 95% CI will be reported at T0 and T1, both for the intervention and control group. Differences in mean change (post- measurements minus baseline) between the intervention group and the control group (interaction group*time) will be calculated. All analyses will be two-tailed and considered significant if α = 0.025. Data will be analysed in SAS, R and IBM SPSS.

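### The 80.27% power is for 6 unmatched homes per arm and appears to use individual-level degrees of freedom; no power is given for the 7 matched pairs planned, and fourteen homes do not match the suggested two extra per arm

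*Protocol article*

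**What the plan says.** **Sample size.** The inputs are "unequal cluster sizes with a coefficient of variation of 0.17 and mean size of 30" and "an intra-cluster correlation coefficient of 0.036". They lead to a design effect of 2.07. With 161 staff per arm in 6 clusters, the design "will achieve 80.27% power to detect an effect size of 0.5 at a significance level of 2.5" per cent. The section limits this calculation to a completely randomised cluster trial with a matching correlation of zero and a constant effect across pairs. It then adds: "To compensate for the loss of degrees of freedom introduced by matching, it is suggested to add two clusters per arm". No power is attached to that addition.

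**Abstract, Methods.** "Fourteen eligible nursing homes will be pair-matched", with one home of each pair randomised to each condition. That is 7 homes per arm.

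**Outcome analysis.** "All analyses will be two-tailed and considered significant if α = 0.025". The model has random slopes for condition and for time by condition at the level of the nursing home pair. The need for the slopes is tested, and they are left out if the model does not converge.

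**The concern.** Two things do not fit together.

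1. The unit of randomisation is the home, so the precision of the treatment comparison is limited by the number of homes or pairs. A power figure that inflates the variance by the design effect, but takes its critical value from a t distribution with about 154 df, leaves out the penalty for having few clusters. With 12 to 14 homes and a 2.5% level, that penalty is large.
2. The protocol recognises that matching costs degrees of freedom and names a remedy, but the planned number of homes is one per arm short of it. The text does not explain the 7.

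The trial has two primary outcomes, each tested at 2.5%. If either result is null, a reader will take 80% as the chance the trial had of finding a 0.5 SD effect. The document offers no other figure.

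**Working it through.** **Inputs.** From Sample size: effect size d = 0.5, ICC 0.036, CV of cluster size 0.17, mean cluster size 30, design effect 2.07, 161 per arm, 6 clusters per arm, matching correlation 0. From Outcome analysis: two-tailed α = 0.025. From the abstract: 14 homes in 7 pairs.

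**Step 1. Reproduce the stated figure.**
- Design effect = 1 + [(CV² × (k−1)/k + 1) × m − 1] × ICC. With m = 30 and k = 6 this is 2.070, as stated.
- Effective n per arm = 161 / 2.07 = 77.8.
- Noncentrality = 0.5 × √(77.8/2) = 3.118.
- Noncentral t, df = 2 × 77.8 − 2 = 153.6, two-sided 2.5%: **80.26%**, against 80.27% stated.

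**Step 2. Same inputs, cluster-level df.** With 6+6 homes, df = 10 and the critical value rises from 2.26 to 2.63. Power is **68.4%**. One other route comes near the stated figure: 10 df with a two-sided 5% test gives 80.20%. The two-tailed 2.5% rule excludes that route for this trial.

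**Step 3. The planned 7 pairs.** Here the design effect is 1 + [(1 + CV²) × m − 1] × ICC and the noncentrality is 0.5 × √(7m / (2 × design effect)). The matching correlation is 0 and there is no gain from baseline. Testing the effect against between-pair variation gives df = 7 − 1 = 6 (critical value 2.97). Ignoring the pairing gives df = 12 (critical value 2.56).

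| Analysed per home (per arm) | Design effect | Noncentrality | Power, 6 df | Power, 12 df |
|---|---|---|---|---|
| 21.8 (152 = 242 × 0.7 × 0.9) | 1.771 | 3.281 | 63.5% | 75.5% |
| 23 (161) | 1.816 | 3.329 | **64.8%** | **76.8%** |
| 30 (210) | 2.075 | 3.557 | **71.0%** | **82.5%** |
| 34.6 (242, all analysed) | 2.245 | 3.671 | 73.9% | 84.9% |

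On 6 df, 80% power needs about 50 analysed staff per home. At 23 per home, 80% power is reached for an effect of about 0.59 SD.

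**Step 4. The 8 pairs that the suggested addition implies** (7 df): 71.2% at 161 per arm, and **80.3%** at 30 per home. So at the protocol's mean cluster size the addition would have restored the target.

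**Step 5. What could raise or lower the 6-df figures.** The protocol gives neither correlation, so these are assumptions.
- *Matching.* If matching removes a share r of the between-home variance, the variance of the difference is 2 × [ICC(1−r) + (1−ICC)/m + ICC × CV²] / 7. Power at 23 and 30 per home is 71.7% and 78.5% for r = 0.3, and 76.7% and 83.8% for r = 0.5.
- *Baseline.* The model tests a difference in change. If 0.5 is in units of the endpoint SD, everyone is measured twice, and the T0–T1 correlation is ρ at both home and individual level, the noncentrality is divided by √(2(1−ρ)). At 23 per home this gives 3.039 and 56% for ρ = 0.4, 3.329 and 65% for 0.5, 3.722 and 75% for 0.6, and 4.298 and 87% for 0.7.

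**The case against.** The strongest defence is that the section is open about its limits. It labels the calculation as one for an unmatched trial, and it says that matching costs degrees of freedom. It never claims 80.27% for the matched design. The arithmetic also reproduces. All of that stands, and it rules out calling the figure a calculation slip. It does not rescue the figure for the unmatched design, where 6+6 homes give 10 df and about 68%. The 154 df is an inference, though the only one found that fits a two-tailed 2.5% test.

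Three stronger readings are tempting, and the documents do not support them.

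- A reader might take 80.27% to rest on 6+2 clusters per arm. It rests on 6. The two extra are a later suggestion with no calculation behind them.
- A reader might conclude that the trial simply has 65% power. That is one point in a range. The 161 per arm is a computed requirement for 6 homes, not a cap, because all eligible staff receive the questionnaire. The 6 df follow from pair-level slopes that the analysis section may drop. Homes are matched on province, facility type and beds, which may remove some between-home variance.
- A reader might infer that the design lacks 80% power for either primary outcome. The protocol does not say whether 0.5 is in endpoint or change SD, and it gives no T0–T1 correlation. High correlations would bring power above 80%. Correlations below 0.5, or staff seen only at T1, would lower it.

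The possible use of 12 df does not support the stated figure in advance, because it depends on a test or a convergence failure in the trial's own data.

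**Conclusion.** The point holds in a limited form. The stated 80.27% is optimistic even for the unmatched design that it describes: about 68% on cluster-level df at two-tailed 2.5%. The suggested 8 homes per arm and the planned 7 contradict each other, whatever model is used. No power is given for the design that will be run.

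On the protocol's inputs, with zero matching correlation and no gain from baseline, 7 pairs on 6 df have about 65% power at 23 analysed per home and 71% at 30. On 12 df these become about 77% and 82.5%. Whether true power reaches 80% depends on respondents per home, df, matching and baseline correlation, and the protocol does not fix all of these. The defect is a stated design property that the planned design has not been shown to have. It is neither a calculation slip nor proof of an underpowered trial.

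**What to change.** In the Sample size section:

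1. Reconcile the 6 clusters of the calculation, the suggested two extra per arm and the fourteen homes of the abstract, and give the reason for 7 per arm.
2. Replace the 80.27% sentence with the power for 7 matched pairs at two-tailed 2.5%, using cluster- or pair-level df. Give it as a range, and state the assumed respondents per home, the df, the matching correlation and the T0–T1 correlation. Say also whether 0.5 is in endpoint or change SD. A workable minimum is the 6-df and 12-df figures at 23 and 30 per home, with one or two matching and baseline scenarios.

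The cost is one paragraph and a less favourable stated power. No extra homes are needed, and conduct and analysis do not change.

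### Inflating 161 staff per group for 70% response and 10% turnover gives 256 (512 in total), not the 242 (484) printed; how far power suffers depends on the design effect used

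*Protocol article*

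**What the plan says.** All the figures are in one paragraph, the Sample size section of the protocol article.

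- Cluster assumptions: "coefficient of variation of 0.17 and mean size of 30 and an intra-cluster correlation coefficient of 0.036", from which "the design effect for a completely randomised cluster randomised trial is estimated at 2.07".
- Requirement before losses: "a sample of 161 staff members for each group across 6 clusters will achieve 80.27% power", for an effect size of 0.5 and a significance level of 2.5%. The Outcome analysis section gives the sidedness: "All analyses will be two-tailed and considered significant if α = 0.025".
- Allowance for losses: the 161 was "increased to 242 staff members per group (total sample size of 484) to allow for an initial response rate of 70" per cent and a staff turnover of 10%.

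The paragraph names no other allowance and gives no inflation formula. It also mentions two further clusters per arm, but ties them to degrees of freedom lost through matching, not to non-response or turnover.

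**The concern.** The paragraph prints the starting number, both loss rates and the result, so the step can be checked directly. The losses come one after the other: some invited staff do not answer at baseline, and some of those who answer leave before follow-up. The usual inflation divides by the product of the two retained fractions, and that does not give 242.

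What is at stake is whether the published sample size delivers the evaluable number that the paragraph says is needed. If 242 per group are approached and both losses occur as stated, fewer than 161 remain, and the printed power figure no longer belongs to the printed sample size.

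**Working it through.** **Inputs (Sample size section unless noted).** 161 per group over 6 clusters; power 80.27%; standardised effect 0.5; alpha 0.025, two-sided (Outcome analysis section); mean cluster size 30; coefficient of variation 0.17; ICC 0.036; design effect 2.07; initial response 70%; turnover 10%; inflated size 242 per group, 484 in total.

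**Step 1: reproduce the plan's base figures.**

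Design effect = 1 + ((CV² + 1) × m − 1) × ICC = 1 + ((0.0289 + 1) × 30 − 1) × 0.036 = 1 + 29.867 × 0.036 = 2.075. The plan states 2.07.

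Effective size per group = 161/2.07 = 77.78. A two-sided two-sample t-test at alpha 0.025 with effect 0.5 and 2 × 77.78 − 2 degrees of freedom gives 80.26% power. The plan states 80.27%. The base calculation therefore reproduces, and this is the method used below.

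**Step 2: the inflation.**

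161/(0.70 × 0.90) = 161/0.63 = 255.6, so 256 per group and 512 in total.

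In reverse, 242 × 0.63 = 152.5 per group, about 9 short of 161. The printed figure is 256 − 242 = 14 per group (28 in total) too low, and 14/256 = 5.5%.

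**Step 3: look for another reading that gives 242.**

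| Reading | Result |
|---|---|
| 161/0.70 × 1.10 | 253.0 |
| 161 × 1.30/0.90 | 232.6 |
| 161 × 1.30 × 1.10 | 230.2 |
| 161 × 1.40 | 225.4 |
| 161/0.60 | 268.3 |
| 161/0.70 (response only) | 230.0 |
| 161/0.90 (turnover only) | 178.9 |
| 161 × 1.50 | 241.5 |
| 161/(0.70 × 0.95) | 242.1 |

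Only the last two come to 242. The first of them is a flat 50% increase. The second uses 5% turnover. Neither matches the stated 70% and 10%.

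**Step 4: power at 152.5 per group, same t-test.**

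| Design effect | Basis | Effective n per group | Power |
|---|---|---|---|
| 2.07 | held at the plan's value | 152.5/2.07 = 73.65 | 77.8% |
| 1.905 | recomputed: 152.5/6 = 25.4 per home | 80.02 | 81.5% |
| 1.771 | recomputed: 152.5/7 = 21.8 per home | 86.1 | 84.5% |

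The recomputed design effects use the formula in Step 1 with the plan's CV and ICC. For 25.4 per home: 1 + (1.0289 × 25.4 − 1) × 0.036 ≈ 1.905. The 7-home row ignores degrees of freedom lost to matching.

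For a like-for-like comparison, recomputing the design effect for the plan's own 161 over 6 homes (26.8 per home) gives 1.958 and 82.6% power. On that convention the loss from 161 to 152.5 is about 1.1 points (82.6% to 81.5%). On the fixed 2.07 it is about 2.5 points.

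**The case against.** The strongest reply is that the shortfall does no harm. The design effect of 2.07 belongs to a mean cluster size of 30. With fewer staff in the same homes the clusters are smaller and the design effect falls, so 152 staff over 6 homes still give about 81.5%, above the stated 80.27%. The Abstract also plans fourteen homes, seven per arm, which would raise the figure to about 84.5% before any cost of matching. In addition, every eligible member of staff in each home is listed and sent a questionnaire (Data collection methods), so the realised sample depends on the homes' staffing more than on whether the article prints 242 or 256.

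Much of this stands, and it limits the consequence. A reader might infer that the trial misses its stated power. The documents do not support that without a condition: the 77.8% requires the design effect to stay at 2.07. Holding it there is defensible, because the plan itself pairs 2.07 with 161 over 6 clusters (26.8 per home), but it is not the only reading.

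A reader might also infer that non-response at T1 cuts the usable sample further. The documents give no T1 response rate. The planned linear mixed model is not restricted to staff with both measurements, and newly hired staff also receive the T1 questionnaire, so counts of complete pairs are not the planned analysis set. Nor does any section say that 484 is the threshold for judging recruitment.

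None of this makes 242 follow from 70% and 10%. New staff may partly replace leavers, but the paragraph itself counts turnover as a loss. Nor is this detail that a condensed article may leave out: the inputs and the result are both printed, and they disagree.

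**Conclusion.** The inflated sample size is wrong as written. With the stated 70% response and 10% turnover, applied one after the other, 161 becomes 256 per group (512 in total), not 242 (484). The printed figure is 14 per group, or 5.5%, too low, and leaves about 152 per group against the required 161. This rests only on figures in the Sample size section and on treating the two losses as sequential; none of the other readings of the stated rates tried here gives 242 either.

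The power consequence is small and conditional: about 77.8% with the design effect fixed at 2.07, about 81.5% with it recomputed for 6 homes. It should not be reported as an established loss of power. The point is a correction to a stated figure; it does not undermine the design.

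**What to change.** Either of two changes would settle it.

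1. Correct the figures to 256 per group and 512 in total. Check: 256 × 0.63 = 161.3, which meets the requirement of 161.
2. Keep 242 and 484, and state that with 70% response and 10% turnover they yield about 152 per group. Give the power that follows and the design effect assumed for it: about 77.8% at 2.07, or about 81.5% at about 1.91 for 6 homes.

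If 242 came from a different allowance, such as a flat 50% increase or 5% turnover, the text should name that allowance in place of the present one.

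The cost is one or two sentences. All eligible staff in the participating homes are already surveyed, so neither recruitment nor the analysis changes.
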